## Discussion

This single-blinded, randomized controlled clinical trial aims to evaluate the efficacy and safety of acupuncture on body weight control in Hong Kong. It will be the first such study on the Hong Kong population and will obtain evidence for utilizing acupuncture in obesity treatment especially for patients with Hong Kong diet patterns and health conditions. In order to achieve a higher therapeutic efficacy, we will integrate electro-acupuncture with auricular acupressure. Except for acupuncture point stimulation on the body and ears, we will not apply any interventions such as CHM, diet or physical activities to the subjects. Therefore, the effects of acupuncture alone will be observed. The outcome measures will include the change in body weight and body fat percentage, which will provide data to us on analysis of the treatment’s potential benefit on body fat mass.

So far there is no study of this kind in Hong Kong. This pilot study will provide evidence for large-scaled research such as combined therapy on overweight subjects with CHM, diet control, physical training or behavioural intervention. Further research on the changes in hormones, the nervous system or psychological conditions can also be developed to specifically target the Hong Kong population, as there have only been overseas studies up to the present.

In this clinical trial, the selection of body and auricular points is standardized and utilized for every subject. This may be helpful for easier utilization of the treatment over different individuals, but the limitation is that the selection of acupuncture points is not based on syndrome differentiation, which is the main concern in traditional Chinese acupuncture. Another limitation is the small sample size, as the trial was proposed to be a pilot study for a later large-scaled clinical trial.

In conclusion, in this pilot study, a single-blinded, randomized controlled clinical trial will be conducted to evaluate the effectiveness, efficacy and safety of acupuncture on weight control in Hong Kong. This study will obtain the solid evidence for Chinese medicine practitioners (CMPs) to utilize acupuncture for obesity and will also provide a platform to offer research training opportunities for junior CMPs.

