## Background

Obesity is an increasingly prevalent chronic condition that is associated with serious morbidity and mortality [1]. According to the statistical data of the Centre for Health Protection, Hong Kong SAR in 2013, 36.6 % of the population aged 18–64 were classified as overweight or obese (body mass index, BMI ≥ 23), including 18.8 % as obese (BMI ≥ 25) among all the population. Excess body weight is the sixth most important risk factor contributing to the overall burden of disease worldwide, such as hypertension, heart disease, hypercholesterolaemia, diabetes mellitus, cerebrovascular disease, gall bladder disease, and some types of cancer [2, 3]. Obesity is becoming a global epidemic and common health problem. The weight control treatments commonly used nowadays include behavioural intervention, dietary intervention and physical activity, which require a higher level of self-discipline and take up to 6 months or longer to achieve significant weight change [4]; surgery like the duodenal–jejunal bypass liner, which may cause surgical complications [5]; and anti-obesity medications.

Currently, most of the Western anti-obesity drugs have adverse effects like oily discharge followed by flatus and faecal incontinence for orlistat [6]; headache, nausea and dizziness for lorcaserin [7] or body weight regaining upon cessation of therapy [8]. More people would like to seek help from Chinese herbal medicine (CHM) and/or acupuncture for body weight control, especially from acupuncture because it is safe and does not involve the intake of drugs [9].

Systematic reviews and randomized controlled trials have shown the beneficial effects of acupuncture, including body acupuncture and auricular acupressure [9, 10]. Acupuncture compared with placebo or lifestyle modification had more effectiveness in lowering body weight, BMI and waist circumference and it had a similar efficacy as the Western anti-obesity drugs with fewer reported adverse effects of insomnia, headache or gastrointestinal reactions [10, 11]. Auricular acupressure has been summarized as having the effect of appetite suppression on overweight patients [12], and its efficacy on weight control is higher when combined with body acupuncture [13].

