#### Inclusion criteria

Patients who meet all of the following criteria will be eligible for the study: men or women aged between 18 and 65 years old; with body mass index (BMI) ≥ 25 kg/m^2^; who have not received any other weight control measures or any medical and/or drug history within the last 3 months.

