#### Sham auricular acupressure

The Semen Vaccariae embedded tape used in the treatment group will be applied on four non-acupoints at the helix unilaterally and retained for 24 hours, and then the alternate ear will be used at the next visit (Fig. 2). The helix region was suggested to be used as a control in auricular needling and was applied in previous clinical trials [19, 20].

All subjects will be advised to have a regular number of meals daily and not to have any snacks. Meals comprise one bowl of rice (210 g) for subjects > 70 kg and two-thirds of a bowl of rice (140 g) for those < 70 kg, with instructions to eat side dishes balanced with the rice. Also, subjects will be instructed not to perform any exercise other than that required for their daily work.

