### Outcome measures

The primary outcome is the change in body weight before and after treatment. The secondary outcomes include changes in BMI, waist circumference, hip circumference and body fat percentage during the treatment and follow-up period. Besides at baseline (0 week), the numbers will be measured every 2 weeks. Both the body weight and body fat percentage will be measured with the Omron Karada Scan HBF-701.

Adverse events will be noted throughout the study, based on participant reports and laboratory tests (whole blood counts, renal and liver functions) if needed. All clinical adverse events will be recorded according to terms of intensity (mild, moderate or severe), duration, outcome and relationship to the study.

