### Data processing and analysis

All efficacy and safety analyses will be conducted according to the intention-to-treat (ITT) principle. Missing values will be imputed by the last-observation-carried-forward method. The statistical analysis will be performed using the Statistical Package for the Social Sciences (SPSS) for Windows version 21.0. The statistical significance is defined as two-sided *P* value of < 0.05. Baseline characteristics will be reported as mean (SD). Baseline differences between the groups will be assessed with the use of Student’s *t* test for normally distributed continuous variables and the non-parametric Mann-Whitney *U* test for non-normally distributed variables. For categorical variables, the chi-squared test or Fisher’s exact test will be used. Comparisons between groups will be conducted by using an analysis of covariance (ANCOVA) with baseline as covariate. All items and subscales will be compared between groups every 4 weeks using ANCOVA, with treatment group as a factor in the model and baseline as the covariate. The changes from baseline to endpoint of treatment in scores will be tested with a repeated measures analysis of variance (ANOVA). Within-group differences will be assessed with a paired *t* test for normally distributed data and a Wilcoxon signed-rank test for non-normally distributed data.

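### The Discussion says no diet or activity intervention is applied, yet all subjects get meal and exercise instructions, so the trial estimates acupuncture over sham added to them

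*Protocol article*

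**What the plan says.** In the protocol article's Discussion, first paragraph, the authors state that apart from stimulating body and ear points "we will not apply any interventions such as CHM, diet or physical activities to the subjects". The next sentence draws the inference: "Therefore, the effects of acupuncture alone will be observed".

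The Interventions section, in the second paragraph under Sham auricular acupressure, gives instructions to both arms: "All subjects will be advised to have a regular number of meals daily and not to have any snacks". It then sets the rice in a meal at 210 g for those above 70 kg and 140 g for those below, with side dishes balanced against it. It adds that "subjects will be instructed not to perform any exercise other than that required for their daily work".

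The Background counts diet and activity as treatments for weight: "The weight control treatments commonly used nowadays include behavioural intervention, dietary intervention and physical activity". Eligibility is restricted to people "who have not received any other weight control measures" in the previous 3 months.

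Under Outcome measures, "The primary outcome is the change in body weight before and after treatment". Data processing and analysis plans between-group ANCOVA with baseline as covariate. Its last sentence adds a second kind of test: "Within-group differences will be assessed with a paired" *t* test, or a Wilcoxon signed-rank test when the data are not normal.

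**The concern.** Two current statements in the same article conflict. A no-snack rule and a rice portion banded by body weight are dietary instructions, and the exercise restriction is an instruction about activity. The Discussion denies any such intervention and rests its reading of the results on that denial.

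Two things are at stake:

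- **What the trial estimates.** A reader would take the result as the effect of acupuncture with no diet component. A planner of the later trial, which the Discussion describes as possibly combining treatment with diet control, would think diet instructions were still to be added.
- **How within-arm change is read.** Weight change in the acupuncture arm mixes acupuncture, meal rules, restricted exercise and time. If the Discussion's sentence is taken at face value, a significant fall in that arm could be reported as acupuncture's doing.

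**Working it through.** **1. The texts side by side.**

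| Topic | Discussion | Interventions |
|---|---|---|
| Diet | none applied | regular meals, no snacks, rice 210 g or 140 g by weight |
| Physical activity | none applied | no exercise beyond daily work |
| Who | the subjects | all subjects, both arms |

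The diet row is a direct conflict. The activity row is weaker, because forbidding extra exercise is not the same as prescribing it, but it is still a study instruction about activity.

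**2. What each analysis estimates.** Let T be change over time, I the effect of the shared instructions, S whatever the sham procedure does, and D what acupuncture adds over sham when the instructions are in force.

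- Mean change, acupuncture arm: T + I + S + D
- Mean change, sham arm: T + I + S
- Between-arm difference: D
- Within-arm change, acupuncture arm: T + I + S + D, not D

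So I cancels from the randomised contrast, but D is defined with the instructions present. It equals the effect without them only if the instructions do not alter what acupuncture does, which the article does not address. A within-arm test addresses the sum of all four terms.

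**3. The SD implied by the sample size.** The Sample size section gives a 1.56 kg difference, 60 subjects (30 per arm), 90% power and alpha 0.05, but no SD, so 60 cannot be reproduced independently. Solving backwards:

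- Normal approximation: SD = 1.56 / [(1.960 + 1.282) × √(2/30)] = 1.86 kg
- Two-sample *t* test (noncentral *t*): SD = 1.83 kg

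**4. Illustration for the paired test.** With 72 enrolled, 36 per arm are analysed under intention to treat with last observation carried forward. On 35 degrees of freedom the critical value is 2.030.

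- Significance threshold at SD 1.83 kg: 2.030 × 1.833 / √36 = 0.62 kg, and 0.62 / 1.56 = 40% of the planning difference
- Threshold at an assumed SD of 3.0 kg: 2.030 × 3.0 / 6 = 1.02 kg

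Set D to zero and let the arm lose m kg for shared reasons. The probability of significance comes from the noncentral *t* with noncentrality m / (SD / 6):

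| m (assumed) | SD 1.83 kg | SD 3.0 kg |
|---|---|---|
| 0 kg | 5% | 5% |
| 0.5 kg | 36% | 16% |
| 0.74 kg | 65% | 30% |
| 1.0 kg | 89% | 49% |

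The 0.74 kg row is only a point on the scale. It is the lower confidence limit quoted in the Sample size section for acupuncture and says nothing about meal advice.

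**5. Check on the between-arm test.** In 20,000 simulated trials with 36 per arm, SD 1.83 kg and the same 1.0 kg loss in both arms, an unadjusted two-sample *t* test rejected in 5.0% and the within-arm test in 89%.

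**The case against.** The strongest reply is that no planned efficacy inference depends on the Discussion's sentence. The objective is acupuncture compared with sham, the sample size uses a two-sample test, and the group comparison is a baseline-adjusted ANCOVA. Identical instructions in both arms help to isolate the acupuncture component. This stands, and a reader who inferred that the instructions bias the randomised result would be wrong.

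Several stronger readings are tempting, and the article does not support them:

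- **That the authors plan to claim efficacy from within-arm change.** The Discussion never mentions the paired tests, and the sentence planning them neither names weight nor attributes anything to acupuncture.
- **That the primary outcome is a within-arm quantity.** The before-and-after wording defines a change score, and the Sample size section takes the same endpoint into a two-sample test.
- **That the rules restrict intake and are new at baseline.** The text sets a portion. It does not say that this is less than subjects usually ate, gives no start date, and does not say that subjects previously snacked or exercised. The 3-month eligibility rule and the absence of a described run-in make a new start plausible, not certain.
- **That the percentages measure harm.** A paired test will detect any non-zero mean change in any parallel trial. The shifts are assumed, all are in the direction of loss, and an exercise restriction could push weight the other way.

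Dropping within-arm P values is also general advice that would apply without the meal rules. That is fair, but here the article supplies a sentence that invites the wrong reading, so the two changes belong together. None of these replies removes the conflict over diet or rescues the inference drawn from it.

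**Conclusion.** The point holds as a correction of interpretation. The statement that no diet intervention is applied is wrong as written, and the conclusion about acupuncture alone does not follow from it. The randomised ANCOVA is sound. It estimates the effect of acupuncture (with auricular acupressure) over sham, added to common meal and exercise instructions. Within-arm changes cannot be attributed to acupuncture.

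No size can be put on the consequence from the documents. The 36%, 65% and 89% figures rest on a back-solved SD of 1.83 kg and on assumed shared losses, and they fall to 16%, 30% and 49% if the SD is 3.0 kg. They show how readily a paired test could be significant without any acupuncture effect, not how often that will happen in this trial. The matter is minor and does not call the design into question.

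**What to change.** 1. **Discussion, first paragraph.** Replace the two sentences with wording such as: *all subjects receive the same meal instructions and are told not to take additional exercise; the trial estimates the effect of acupuncture over sham acupuncture added to these instructions.*
2. **Discussion, second paragraph.** Where diet control is named as part of later combined therapy, note that diet instructions were already in place in this trial.
3. **Data processing and analysis.** Replace the within-group paired *t* and Wilcoxon tests with the mean change and 95% CI in each arm, labelled as description, and say that the efficacy conclusion rests on the between-arm ANCOVA.

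The cost is a few sentences and the loss of within-arm P values. Participants, visits, instructions and sample size are unchanged. Trial status reports that recruitment is still under way, so the change can be made before analysis.

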### Trial status

The participants are currently being recruited for the present study.

## Abbreviations

ANCOVA, analysis of covariance; ANOVA, analysis of variance; BMI, body mass index; CHM, Chinese herbal medicine; CMP, Chinese medicine practitioner; ITT, intention-to-treat
